## **2. STUDY OBJECTIVES**

### **2.1 Primary Endpoints:**

- Seroconversion and seroprotection rates and mean GMT increases in haemagglutination inhibition titres 21-28 days post-immunisation for each of the three included vaccine strains

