**9.4 Efficacy analysis**

All continuous data will be described by means of summary statistics: N, mean, standard deviation, minimum, median and maximum and 95% confidence intervals. Categorical variables will be presented using the number of observations (N), frequencies (%) and missing data.

The efficacy variables will be described by adequate methods in tables by visit and treatment group. The change from baseline to endpoint (if necessary defined as the last

value carried forward) will also be described by summary statistics. Influenza-specific antibody titres (IgM, IgG, IgG1-4, haemagglutinin inhibition (HI) titre) will be analysed by calculating changes from the background pre-immune serum readings.

All individuals with at least one post-baseline measurement for efficacy will be included in the efficacy population. The analysis will include listings of objective response according to currently pertaining TGA influenza vaccine criteria, (e.g. seroconversion = four fold increase in HI over baseline, seroprotection = post-immunisation HI of 1:40 or greater; potency = fold increase in HI geometric mean titres (GMT). GMT and 95% confidence intervals will be estimated pre- and post-immunisation and compared across groups by ANOVA. The proportion of each vaccine group achieving seroconversion or seroprotection will be compared by Fisher's exact test.

An efficacy analysis to identify differences in treatment response between unadjuvanted and adjuvanted TIV groups and between needle and needless injector groups will be performed on the complete PPP irrespective of age. Additional subgroup efficacy analyses to identify significant differences in treatment response between unadjuvanted and adjuvanted TIV groups and between needle and needless injector groups will be performed stratifying subjects by age.

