All enrolled individuals who received at least one dose of treatment will be included in the safety population. The analysis will include listings and frequency tables of adverse events and laboratory values graded according to the FDA/CBER vaccine toxicity grading scale. Adverse events will be tabulated by time (day) and by severity (mild, moderate and severe). Clinically significant reactions will be defined as measured local reactions >10mm, fever >38°C and severity  $\geq$  moderate for other symptoms. Severe reactions are defined as measured local reactions >50mm, fever >39°C and severity  $\geq$  severe for all other symptoms. Injection site reactions will be combined to give an “any local” reaction category and all other symptoms combined to give an “any general” reaction. The proportion of subjects having an adverse reaction will be estimated by vaccine group, observation period and severity. Subjects will be asked to score injection site pain at the time of injection, and 30 minutes post immunization using a visual analogue scale. Binomial distribution point estimates and 95% confidence intervals will be used to estimate each rate. Percentages will be compared by Fishers exact test.  $P < 0.05$  will be considered statistically significant. No adjustments will be made for multiple comparisons.

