### **9.8 Subgroup analyses**

A pooled efficacy analysis will be performed on the total study efficacy population. In addition, subgroup analyses of vaccine response rates will be performed stratifying responses according to the subject age and analysis of differences in GMT by ANOVA and seroconversion and seroprotection rates by Fishers exact test.

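### The age-subgroup analyses in sections 9.4 and 9.8 look for significance separately within each age group, which cannot show whether the vaccine or device effect differs by age

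*Protocol*

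**What the plan says.** Section 9.4 first plans the adjuvant and device comparisons on all ages together; these "will be performed on the complete PPP irrespective of age". It then adds "Additional subgroup efficacy analyses to identify significant differences in treatment response between unadjuvanted and adjuvanted TIV groups and between needle and needless injector groups", which "will be performed stratifying subjects by age".

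Section 9.8 repeats the plan and names the method: "stratifying responses according to the subject age and analysis of differences in GMT by ANOVA and seroconversion and seroprotection rates by Fishers exact test". Neither section names a treatment-by-age test.

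The endpoints come from section 2.1: "Seroconversion and seroprotection rates and mean GMT increases in haemagglutination inhibition titres 21-28 days post-immunisation for each of the three included vaccine strains".

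Section 9.3 says that all variables are analysed descriptively. The only significance threshold in the document, P<0.05, is in section 9.6, Safety analysis, where it "will be considered statistically significant. No adjustments will be made for multiple comparisons".

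**The concern.** The protocol settles both a purpose (finding significant differences by age group) and a method (the same tests repeated within each stratum). A result that is significant in one age group and not in another is not evidence that the effect differs between them. Each stratum has less power than the whole trial, so two strata with the same true effect can easily fall on opposite sides of the threshold.

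At stake is how an age-specific result would be read. If the adjuvant appears to work only in older or only in younger subjects, the text offers no analysis that could separate a real difference from a chance split. Sections 9.3 and 9.4 also disagree on whether these analyses are descriptive or a search for significance, so a reader cannot tell what weight they are meant to carry.

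**Working it through.** **The plan's own figure.** Section 9.7 starts from a minimum of 50 per group and allows 20% dropout: 50 / 0.8 = 62.5, so 63. The plan takes 65, which gives 65 × 0.8 = 52 evaluable per group, and 6 × 65 = 390 in all, within the limit of 400. The sample size is consistent. No power or error rate is stated for the age analyses, so there is none to reproduce.

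**Inputs from the protocol.** Six groups (three vaccines by two devices, section 5.2) and 52 evaluable per group. Unadjuvanted vaccine therefore has 2 × 52 = 104 subjects, and the two adjuvanted formulations pooled have 4 × 52 = 208.

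**Assumptions, because the protocol gives no value.** Two age groups of equal size (52 v 104 in each), the adjuvanted groups pooled, one strain's seroconversion rate, two-sided P<0.05, and the response rates shown below.

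**Formula.** Let h be the exact power of Fisher's test in one age group, found by enumerating all outcomes. The true effect is the same in both groups and the groups are independent, so the chance that exactly one is significant is 2h(1 − h).

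| True rates (unadjuvanted v adjuvanted) | Power, all ages | h, each age group | Exactly one significant |
|---|---|---|---|
| 50% v 55% | 0.115 | 0.072 | 13% |
| 50% v 60% | 0.358 | 0.181 | 30% |
| 50% v 65% | 0.696 | 0.379 | 47% |
| 50% v 70% | 0.919 | 0.636 | 46% |
| 50% v 75% | 0.990 | 0.854 | 25% |
| 50% v 80% | 1.000 | 0.962 | 7% |
| 60% v 75% | 0.744 | 0.452 | 50% |
| 60% v 85% | 0.997 | 0.908 | 17% |

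For example, at 50% v 65%: 2 × 0.379 × 0.621 = 0.471.

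**Other contrasts and splits, at 50% v 65%.**
- Unadjuvanted vaccine against one adjuvant dose (52 v 52 per age group): h = 0.295, and 2 × 0.295 × 0.705 = 42%.
- Device contrast (78 v 78 per age group): h = 0.408, and 2 × 0.408 × 0.592 = 48%.
- Pooled contrast with a 25/75 age split: stratum powers 0.197 and 0.567, and 0.197 × 0.433 + 0.567 × 0.803 = 54%.

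For equal halves, 2h(1 − h) cannot exceed 50%. It peaks where each age group has about even power and falls away for very small or very large effects.

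**Number of tests.** Three measures × three strains = 9 endpoints. With two contrasts and two age groups that is 9 × 2 × 2 = 36 tests. If they were independent and each at a true 5%, the chance of at least one false positive would be 1 − 0.95^36 = 84%. The measures and strains are correlated and Fisher's test is conservative, so the real figure is lower. It depends on correlations and rates that the protocol does not give, so the conclusion does not rest on it.

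**The case against.** Several points on the other side are sound.

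- **No age claim is announced.** A reader might infer that a chance split will be presented as an age-specific benefit. The documents do not support that. No objective or endpoint concerns age, and no rule says that a within-stratum result will lead to a claim. Section 1.2.1 speaks of populations at high risk without mentioning age. Misreading is a risk, not a stated intention.
- **The threshold is inferred.** A reader might also say that each age group is tested at a full, unadjusted 5%. P<0.05 and "No adjustments will be made for multiple comparisons" stand only in the safety section. They are the only candidates for what significant means in section 9.4, but sections 9.4 and 9.8 do not cite them.
- **The analyses are already secondary in rank.** They are called additional subgroup analyses, they sit beside an all-ages analysis, and section 9.3 describes everything as descriptive.
- **A statistical analysis plan may hold the missing detail.** Age cut-points, an interaction model or an exploratory label could be there. Their absence from the protocol is not an error in itself.
- **The size depends on the assumed effect.** Quoting only the scenarios near 50% would overstate the problem.

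What survives is the part that the protocol itself fixes: a search for significant differences by separate tests within age groups. An analysis plan that follows this wording inherits the weakness, and the descriptive label in section 9.3 conflicts with the wording without removing it.

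**Conclusion.** The point holds in a limited form. Sections 9.4 and 9.8 set out within-stratum significance tests for the adjuvant and device contrasts, and these cannot show whether either effect differs by age. They also sit badly with the descriptive status given in section 9.3.

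Under the stated assumptions (two equal age groups, pooled adjuvanted against unadjuvanted vaccine, one strain's seroconversion, P<0.05 carried over from the safety section), a constant true effect leaves exactly one age group significant in about 7% to 50% of trials. It is common for moderate effects and uncommon for very large ones. The all-ages analysis is not affected.

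**What to change.** In sections 9.4 and 9.8:

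- delete the aim of identifying significant differences from the age analyses and label them exploratory, which also brings them into line with section 9.3;
- use age groups stated in advance;
- report the effect in each age group with a 95% CI, for the adjuvant and the device contrast;
- assess any difference by age with a treatment-by-age interaction term, in a log-titre model for GMT and a logistic model for the seroconversion and seroprotection rates;
- state that no age-specific conclusion will rest on a within-stratum P value;
- state that the interaction tests are themselves exploratory and not adjusted for multiplicity. Nine endpoints by two contrasts give 18 such tests; if independent, the chance of at least one false positive is 1 − 0.95^18 = 60%, so a lone significant interaction should not be treated as a finding.

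The change is one of wording and one model term. Date of birth is already recorded (sections 8.2 and 9.10), and no extra subjects are needed. The downside is low power: with two equal age groups each stratum effect has about twice the variance of the overall effect, so their difference has about four times that variance and twice the standard error. The sponsor also gives up calling a single age group's result significant.

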### **9.6 Safety analysis**

All adverse events will be summarized and listed with a detailed description, using the MedDRA dictionary. Frequencies of adverse events (number of patients with the event, number of mentions of the event and percentage of patients exhibiting the event) for each vaccine formulation and immunisation route will be given for all adverse events. Adverse events will be summarized by vaccine formulation and immunisation route, body system and relationship to study drug and severity. In addition, listings will be prepared for adverse events leading to treatment discontinuation and for SAEs.

The vital signs (sitting blood pressure, heart rate and temperature) will be presented with summary statistics over the visits and for the change from baseline to endpoint. Individual laboratory variables over the visits and the change from baseline to endpoint will be listed with summary statistics for each dose level. The frequencies of laboratory values below, within and above the relevant normal ranges will be given. The baseline and endpoint laboratory variables will be presented using a contingency table to investigate any range changes. The abnormal and clinically significant laboratory variables will be presented for each patient over the assessments.

All enrolled individuals who received at least one dose of treatment will be included in the safety population. The analysis will include listings and frequency tables of adverse events and laboratory values graded according to the FDA/CBER vaccine toxicity grading scale. Adverse events will be tabulated by time (day) and by severity (mild, moderate and severe). Clinically significant reactions will be defined as measured local reactions >10mm, fever >38°C and severity  $\geq$  moderate for other symptoms. Severe reactions are defined as measured local reactions >50mm, fever >39°C and severity  $\geq$  severe for all other symptoms. Injection site reactions will be combined to give an “any local” reaction category and all other symptoms combined to give an “any general” reaction. The proportion of subjects having an adverse reaction will be estimated by vaccine group, observation period and severity. Subjects will be asked to score injection site pain at the time of injection, and 30 minutes post immunization using a visual analogue scale. Binomial distribution point estimates and 95% confidence intervals will be used to estimate each rate. Percentages will be compared by Fishers exact test.  $P < 0.05$  will be considered statistically significant. No adjustments will be made for multiple comparisons.

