### OBJECTIVES:

The primary objective is to assess the safety, tolerability and efficacy of an trivalent seasonal influenza vaccine formulated with Advax™ adjuvant by comparison to the trivalent seasonal influenza vaccine alone. A secondary objective is to assess the utility and patient acceptability of a needleless vaccine injector (Pharmajet) by comparison to a standard intramuscular injection with syringe and needle.

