#### Primary Endpoints:

- **Efficacy:** Seroconversion and seroprotection rates for each included serotype
- **Safety:** Adverse events and vaccine tolerability

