## **FULL PROTOCOL**

### **1. INTRODUCTION**

#### **1.1. Background**

Influenza is a highly contagious and potentially deadly disease that can be spread through coughing or sneezing. It is caused by a virus and is not the same as a common cold. It can cause serious and debilitating complications such as pneumonia, especially in the elderly, young children and those with chronic disease.

The current study is designed to establish the safety and efficacy of the standard commercial trivalent inactivated influenza vaccine (TIV) when formulated with a range of adjuvant doses. We have shown in previous studies that addition of Advax™ adjuvant with various seasonal (TIV) or pandemic (H1N1/2009) influenza, or hepatitis B antigens improved the immunogenicity of these vaccines as assessed by higher antibody titres. This is the basis for extending study of Advax™-adjuvanted influenza vaccine to compare adjuvant doses lower to those previously tested and thereby identify the minimum adjuvant dose required for maximal vaccine enhancement.

Seasonal influenza vaccines are currently administered by intramuscular injection using a syringe and needle approach. New technology has made available a needleless injection system that is able to deliver the vaccine utilising a spring powered energy source to create a fine high velocity jet of liquid that directly penetrates through the skin without the use of a needle. The PharmaJet injector which is already approved for human use by the US Food and Drug Administration (FDA) employs a single-use, sterile, auto-disable needle-free cartridge which results in an superior injection experience for children and needle phobic subjects compared to use of needle-bearing syringes. This technology offers major advantages for both administrator and recipient over existing needle injection approaches and hence we plan to randomise trial subjects to receive their vaccine through either the PharmaJet device or needle and syringe, thereby allowing us to assess the influence on patient satisfaction and comfort of receiving their influenza vaccine through a needleless device.

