### **1.2.2 Rationale for schedule and route of administration**

The goal for influenza vaccination is to achieve a protective immune response in a minimum time frame and with the simplest dosing schedule. Animal data using several different models show that there is an increase in both the magnitude of the antibody response as the dose of antigen and adjuvant is increased to a critical levels but beyond this level the antibody response plateaus whilst the risk of adverse reactions continues to rise in a dose dependent manner. Hence it is critical to perform dose ranging studies to identify this “sweet spot” in the antigen and adjuvant dose response. Whilst previous clinical studies have compared different antigen doses, a fixed 20mg dose of Advax™ adjuvant was used. Hence there remains a need to be addressed in this study to now test different doses of adjuvant while keeping the dose of antigen fixed.

New technology has made available a needleless injection that delivers the vaccine through an intramuscular route without the use of a needle, instead utilising a spring powered energy source to inject liquid directly through the skin. The PharmaJet injector

employs a single-use, sterile, auto-disable needle-free syringe that results in an arguably superior injection experience and sensation compared to needle-bearing syringes. This device is FDA approved. Based on the above, we will trial a one dose regime of seasonal influenza vaccine delivered using standard needle and syringe or the PharmaJet needleless injector in a 1:1 ratio for all groups. This will enable us to assess patient satisfaction when using a needleless injector compared to needle-bearing vaccination administration.

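### Reaction rates are to be compared with TIV by P value alone; without an interval for the between-arm difference, section 9.6 cannot support a favourable comparative tolerability statement, mainly for uncommon or severe reactions

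*Protocol*

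**What the plan says.** The Objectives in the protocol synopsis make safety comparative: "The primary objective is to assess the safety, tolerability and efficacy of an trivalent seasonal influenza vaccine formulated with Advax™ adjuvant by comparison" with the unadjuvanted vaccine. The synopsis lists "Adverse events and vaccine tolerability" as the primary safety endpoint.

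Section 9.6 fixes how reaction rates are analysed. Each rate gets a binomial point estimate and a 95% confidence interval. Arms are then compared as follows: "Percentages will be compared by Fishers exact test". P below 0.05 counts as significant, and multiplicity is not adjusted for. Section 9.6 also defines the categories: any local, any general, clinically significant and severe. It mentions no difference or ratio of reaction rates, no interval for either, and no largest acceptable excess.

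Three other places bear on the point:
- Section 9.3 calls the analysis descriptive.
- Section 9.5 compares visual analogue pain scores across groups by ANOVA.
- Section 9.7 sets 65 subjects in each of six groups, taken from a regulatory minimum for antibody responses, and expressly does without a power calculation.

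**The concern.** The primary safety question is how much more reactogenic, if at all, adjuvanted TIV is than TIV alone. The planned output answers two other questions: how precisely each arm's own rate is known, and whether the arms differ detectably. Neither says how large an excess the data still allow.

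This matters most if the result is favourable. Section 1.1 already expects Advax to give its benefit without added reactogenicity, so a statement that it was well tolerated relative to TIV is foreseeable. If the only comparative result behind that statement is a P value of 0.05 or more, it has no support, because group size was not chosen with any reaction rate in mind. A difference with its interval is the quantity that the objective asks for, and it needs no extra data.

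**Working it through.** **Inputs from the protocol**
- Six groups of 65 (9.7), with three formulations allocated 1:1:1 and two routes 1:1 (5.2). This gives 6 × 65 = 390 in total, 2 × 65 = 130 per formulation with routes pooled, and 260 for both Advax groups together.
- The safety population is everyone vaccinated (9.2.1), so the dropout allowance for the last blood sample is not taken off.
- Fisher's exact test at 0.05 (9.6). Sidedness is not stated; two-sided is assumed.

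**Input assumed.** The reaction rate under TIV. The protocol gives none, so a range is shown.

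**The plan's own figure.** 50 / (1 − 0.20) = 62.5, rounded up to 63. The stated 65 is consistent with this, since 65 × 0.80 = 52, which is at least 50. The group size therefore holds for its antibody purpose. It was not derived from safety.

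**Chance of missing a true doubling.** Let X and Y be the numbers of subjects with a reaction in the TIV and Advax arms, independent binomials with rates p and 2p. Power is the sum of P(X = x)·P(Y = y) over all pairs (x, y) for which the two-sided Fisher P is below 0.05. The miss rate is 1 − power. Full enumeration gives:

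| True rates, TIV to Advax | 130 v 130 (one dose group, routes pooled) | 130 v 260 (both dose groups) | 65 v 65 (one dose group, one route) |
|---|---|---|---|
| 2% to 4% | 93% | 88% | 99% |
| 5% to 10% | 75% | 64% | 90% |
| 10% to 20% | 44% | 29% | 72% |
| 15% to 30% | 20% | 9% | 54% |
| 20% to 40% | 7% | 2% | 36% |
| 30% to 60% | 0.2% | below 0.1% | 9% |

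With routes pooled, misses are frequent only when the TIV rate is about 10% or less. Rises short of a doubling can be missed at higher rates too: 20% to 30% is missed 59% of the time at 130 v 130.

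**What an interval adds: an invented result, 22/130 (Advax) v 13/130 (TIV)**
- Fisher P = 0.145, so not significant.
- p1 = 0.1692, Wilson limits 0.1145 to 0.2430. p2 = 0.1000, Wilson limits 0.0594 to 0.1636. Difference d = 0.0692.
- Newcombe lower limit: d − √[(p1 − l1)² + (u2 − p2)²] = 0.0692 − √(0.0547² + 0.0636²) = 0.0692 − 0.0839 = −0.0147.
- Newcombe upper limit: d + √[(u1 − p1)² + (p2 − l2)²] = 0.0692 + √(0.0737² + 0.0406²) = 0.0692 + 0.0842 = 0.1534.

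The interval runs from −1.5 to +15.3 percentage points. The P value alone hides that an excess of 15 points in 100 has not been excluded.

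**A rarer reaction: 14/130 v 7/130, an observed doubling.** P = 0.17, the difference interval is −1.4 to +12.4 points, and the risk ratio interval (log method) is 0.83 to 4.79.

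**The case against.** **There is no pass rule.** A reader might infer that the protocol would accept a doubling of reactions as showing no difference. It does not say so. Section 9.6 defines only what is significant, and 9.3 calls the analysis descriptive. This objection stands. The point is about what the planned output can support, not about a decision rule. A descriptive aim also calls for an effect estimate with its interval.

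**The aim is modest.** Section 1.1 describes a study "designed to establish the safety and efficacy of the standard commercial trivalent inactivated influenza vaccine (TIV) when formulated with a range of adjuvant doses", which invites the reading that the trial must prove safety. That is introduction wording; the formal objective says assess. This also stands, and nothing here relies on the stronger verb.

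**This is detail for a statistical analysis plan.** That is true of the type of interval and the exact list of contrasts. It is less true of the main choice, since 9.6 itself names the estimate (per arm) and the comparison (a P value). Nothing there forbids a difference interval, however.

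**Doublings are not generally missed.** Correct. At 20% or more under TIV, with routes pooled, at most 7% are missed. The composites, any local and any general, cannot be rarer than their components and so are the least affected.

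**Other material exists.** Pain scores are compared by ANOVA, so Fisher's test is the only stated comparison of reaction percentages, not of tolerability as a whole. Per-arm intervals do convey imprecision: in the first example the exact limits are 10.9% to 24.5% and 5.4% to 16.5%. They do not give the limit on the excess, however. Setting the extremes against each other gives 24.5 − 5.4 = 19.1 points, against 15.3 from the proper interval. A careful reader could compute that interval from the counts, which keeps the defect modest.

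**Dose order.** Section 1.2.2 says that "the risk of adverse reactions continues to rise in a dose dependent manner", which might suggest that a trend test should be the main comparison. That sentence reports animal data on antigen and adjuvant dose together, and a trend test would be another P value that puts no bound on harm. It is not part of this point.

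**Conclusion.** The point holds in limited form. Safety is a primary, comparative objective, and for reaction rates the stated method stops at per-arm intervals and a test of difference. A non-significant test at these sizes could not support a favourable comparison for reactions with a TIV rate of about 10% or less: the miss rate for a doubling is 44% or more at 130 v 130 and 72% or more at 65 v 65. For common reactions with routes pooled, the test is adequate against a doubling.

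The figures rest on assumed background rates, a two-sided test, the full 65 per group and complete reaction data. The documents do not support saying that the trial will declare equal safety from P of 0.05 or more, or that relevant harms will be missed whatever their frequency. This is an improvement that should be made to the analysis text; it is not a flaw in the design.

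**What to change.** In section 9.6, for any local, any general, clinically significant and severe reactions, add the risk difference from TIV with a 95% confidence interval (for example Newcombe), for each Advax dose group and for both pooled. Add one sentence saying that comparative tolerability conclusions rest on this interval and not on P of 0.05 or more. Fisher's test and the per-arm intervals can stay. A trend test across the ordered dose groups may be added as an optional supplementary analysis, not as the main between-arm test.

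The cost is about two sentences and a few table columns, with no new data, visits or subjects. The downside is that some tolerability statements will be weaker, especially for severe reactions, where the intervals will be wide relative to the rates.
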